### 6.3 PROCEDURES FOR ELICITING REPORTS OF AND FOR RECORDING AND REPORTING ADVERSE EVENT AND INTERCURRENT ILLNESSES

The following information should be present to complete AE and SAE forms during the initial report (on the day of finding out about the event):

- Description of the event
- Date of onset and resolution (if known)
- Severity
- Assessment of expectedness (is the event anticipated in terms of nature, severity, or frequency) given (a) the research procedures that are described in the IRB protocol and informed consent document; and (b) the characteristics of the subject population being studied
- Assessment of relatedness to study drug
- Any actions taken

Following the initial report, additional information may need to be gathered to complete the AE and SAE forms and to evaluate the event for relatedness. This process may include obtaining hospital discharge reports, physician records, autopsy records or any other type of records or information necessary to provide a complete and clear picture of the SAE and events preceding and following the event.

#### **SAE Reporting:**

If the SAE is not resolved or stabilized at this time or new information becomes available after the SAE form is completed the SAE form should be updated as soon as possible. Any changes or updates to the SAE form must be re-reviewed and re-authorized by the study clinician.

The site must actively seek information about the SAE until the SAE is resolved, stabilized or until the participant is lost to follow-up and terminated from the study.

To summarize: upon determining an Adverse Event is Serious, the following procedures must be followed:

- The study staff, while meeting/talking with the participant or person providing details on the event, gather as much information about the event from the participant as possible and complete the appropriate forms.
- The completed AE and SAE forms are reviewed by key personnel on the Pavlov team (i.e. Site PI or designee). Any relevant clinical documents (labs, physician notes) available at that time are provided to key personnel on the Pavlov team (i.e. Site PI or designee) within 24 hours of finding out about the event.

- After initial notification, the SAE is updated with any additional information.

All unanticipated problems (UPs) must be reported to the US team immediately. The US team must report all UPs to the BUMC IRB and NIAAA within 48 hours of discovering their occurrence.

AEs and SAEs will be reported to the URBAN ARCH DSMB every six months.

#### **6.4 THE TYPE AND DURATION OF THE FOLLOW-UP OF PARTICIPANTS AFTER ADVERSE EVENTS**

All non-mild adverse events (including serious adverse events) will be followed until the event is resolved, stabilized, or until the end of individual's participation in the study.

Site PI or designee will determine a follow-up plan on a case-by-case basis based on their clinical judgment.

#### **6.5 UNBLINDING PROTOCOL**

Participants could be unblinded in the event of an urgent medical need, as determined by the clinician evaluating the participant.

The following are examples of events that may result in emergency unblinding:

-An SAE occurs that is thought to be most likely or definitely related to the study drug.

-An AE or SAE occurs and the clinician treating the patient concludes that knowledge of the treatment arm is necessary to determine the therapy provided to the patient.

-The study drug is accidentally ingested by a child.

[figure not shown]

## 6.6 DATA SAFETY AND MONITORING BOARD

The Data and Safety Monitoring Board (DSMB) was set up to monitor the URBAN ARCH Cohort studies (i.e., Uganda, Russia, Boston) and Intervention trials (i.e., ZINC). The DSMB serves in an advisory capacity to the study PIs and the National Institute on Alcohol Abuse and Alcoholism (NIAAA) to monitor participant safety, data quality and evaluate the progress of the studies conducted under the URBAN ARCH consortium funded by NIAAA.

The DSMB is responsible for ensuring participant safety (by reviewing blinded and unblinded safety data on a regular basis and assessing the safety of study procedures) and for monitoring the overall conduct of the study.

The DSMB will be required to provide recommendations about starting, continuing, temporarily or permanently suspending the trial. In addition, the DSMB will be asked to make recommendations, as appropriate, about:

- Benefit/risk ratio of procedures and participant burden
- Selection, recruitment, and retention of participants
- Protocol violations and adherence to protocol requirements
- Completeness, quality, and analysis of measurements
- Amendments to the study protocol and consent forms
- Participant safety
- Notification of and referral for abnormal findings

## **7. DATA MANAGEMENT**

### **7.1 DATA COLLECTION**

The majority of study data will be captured electronically via a secure, web-based data capture system with the exception of: TLFB data, which will be collected on paper calendars and data on drug and alcohol use disorders, which will be captured on paper, scanned and read in using TELEform software.

### **7.2 QUALITY CONTROL PROCESS**

Quality control measures will include: detailed and unambiguous specifications for completion of data forms, including rules for coding skipped questions and missing data, training of study staff responsible for data collection and built-in validation rules, error checks, question skips for electronic data capture, and computer algorithms to check for out-of-range codes and internal inconsistencies. All data, regardless of capture method, will be converted to SAS datasets and reviewed for logic, skip patterns, response ranges, out-of-range codes, and internal inconsistencies. The RAs will be queried monthly regarding any noted inconsistencies.

### **7.3 DATA SECURITY AND CONFIDENTIALITY**

Screening forms and most other research paperwork will not include the participant's name. Instead a unique ID will be assigned to each person screened; then another number will be assigned to those who enrolled. There will be a master list of names and identification numbers. The master list of study participants will be destroyed seven years after the completion of study analyses and publication of all study manuscripts. Any documents with identifiable participant data will be accessible only to the Russian Co-Investigators, the Russian project manager, and the RA assessors who will be recruiting and following participants.

Tracking information will be kept similarly. Computer data will be password protected, and accessible only to those needing the information for follow-up purposes.

The BDM Core of the URBAN ARCH Consortium designed, developed and will maintain the electronic data collection forms, participant and data tracking, and underlying SQL database systems, and will implement procedures for data quality control, including multiple checks for entered data. Electronic data collection forms are designed to read easily, have clear instructions, preprogrammed skip patterns, real-time range checks and internal logic to minimize missing data and resulting in "cleaner" data at capture. The website and accompanying database are located on secure, password-protected servers, behind the BU firewalls. The BDM Core has access to two Unix servers, including a Linux Beowulf cluster currently configured

with 118 CPUs, as well as an SMP Linux server with 4 x Six-Core AMD Opteron processors (a total of 24 cores x 2.4 GHz each), 64 GB of RAM, and 6 TB (4TB usable) storage capacity. Additionally, the DCC has three dedicated servers, all of which are dual processors with 150 gigabytes for data storage: an SQL database server; a server used for Web site development and management, running Internet Information Server for web page hosting; and a server used for web development pre-production testing environment. The web and database servers use Secure Socket Layering (SSL) to ensure data security and confidentiality. Two fax servers and additional server and a flatbed scanner comprise the Teleform® system. Servers incorporated RAID hard drives for data redundancy. A separate web server dedicated for Cold Fusion applications is also available.

#### 7.4 WEB SYSTEMS

The study will use two web systems: a computerized tracking system and CASIC (for assessment). The computerized tracking system will contain all participant tracking details. This system is web-based, allowing multiple users to access the system. Study forms will be completed according to the schedule below.

|                                        | Screen A | Screen B & Baseline Visit |          | 6-Week | 12-Week | 6-Month | 9-Month | 12-Month | 15-Month | 18-Month | As Needed |
|----------------------------------------|----------|---------------------------|----------|--------|---------|---------|---------|----------|----------|----------|-----------|
|                                        |          | Screen B                  | Baseline |        |         |         |         |          |          |          |           |
| Screener A                             | X        |                           |          |        |         |         |         |          |          |          |           |
| Screener B                             |          | X                         |          |        |         |         |         |          |          |          |           |
| Consent and enrollment form            |          |                           | X        |        |         |         |         |          |          |          |           |
| Contact info                           |          |                           | X        | X      | X       | X       | X       | X        | X        | X        |           |
| Phlebotomy form                        |          |                           | X        |        |         | X       |         | X        |          | X        |           |
| Processing form Pasteur                |          |                           | X        |        |         | X       |         | X        |          | X        |           |
| Processing form IBS                    |          |                           | X        |        |         |         |         |          |          | X        |           |
| Assessment (CASIC and Web)             |          |                           | X        | X      | X       | X       | X       | X        | X        | X        |           |
| Randomization Page                     |          |                           | X        |        |         |         |         |          |          |          |           |
| Medication visit checklist (CASIC)     |          |                           | X        | X      | X       | X       | X       | X        | X        | X        |           |
| Baseline Symptom Monitoring (CASIC)    |          |                           | X        |        |         |         |         |          |          |          |           |
| Medication collection (Paper)          |          |                           | X        | X      | X       | X       | X       | X        | X        | X        |           |
| Baseline tracking form                 |          |                           | X        |        |         |         |         |          |          |          |           |
| Symptom monitoring (Follow-up) (CASIC) |          |                           |          | X      | X       | X       | X       | X        | X        | X        |           |
| Follow-up tracking form                |          |                           |          | X      | X       | X       | X       | X        | X        | X        |           |
| Participant tracking overview          |          |                           |          |        |         |         |         |          |          |          | X         |
| Study conclusion form                  |          |                           |          |        |         |         |         |          |          |          | X         |
| AE/SAE form                            |          |                           |          |        |         |         |         |          |          |          | X         |
| Pre-enrollment contact log             |          |                           |          |        |         |         |         |          |          |          | X         |
| Contact log                            |          |                           |          |        |         |         |         |          |          |          | X         |

012 Electronic forms to be completed at screening and enrollment:

- 013 • Screening Consent: The script that the research assessor reads to potential participants,  
014 describing the purpose of the study and what would occur during the screening.
- 015 • Screener A: This will be completed once a participant gives verbal consent to be screened. It  
016 confirms participant eligibility for the study.
- 017 • Screener B: This will be completed at the baseline visit to confirm that the participant is HIV-  
018 positive, ART-naïve and not pregnant or breastfeeding. This requires the RA to verify the  
019 participant's HIV status (either past HERMITAGE participant; HIV/VL/CD4 test result; medical  
020 records/summary page; doctor's letter). The participant will be asked if they are currently  
021 taking or had ever taken ART. A participant's ART naïve status will require documentation  
022 from the participant's medical record/summary page or a doctor's letter.

023 Electronic forms/documents just for those who are enrolled:

- 024 • Informed Consent: A copy will be maintained at PSMU and the participant will receive a copy.

- Consent and Enrollment Tracking Form: This will be completed in the presence of the participant, after the informed consent is signed. It will generate the participant ID number. This form will allow the assessor to confirm that the participant was enrolled and to enter the answers to the permissions marked by the participant on the consent form (storage of blood for clinical, virological, and immunological studies related to HIV disease and other associated illnesses; contact to use blood for studies not listed above; post-study contact for future research).
- Contact Information/Locator Form: This form will contain the phone number, email address, and physical address of the participant and several additional friends or family contacts to facilitate the follow-up process (the minimum required information is the contact details for the participant and 2 friends or family members). If the participant cannot give the required contact information they must be unenrolled from the study. Assessor will confirm that the phone numbers provided are valid in the presence of the participant.

## Tracking system

### Forms

- Baseline Tracking Form: This will be completed on the day of the baseline visit, after the baseline assessment is administered to the participant. It will track that the participant was sent for a blood draw and that a resource card and compensation was provided to the participant.
- Follow up Tracking Forms: This will be completed on the day of each follow up assessment after the assessment is administered to the participant. It will track the completion of the follow up assessment, blood draw, and compensation.
- Participant Tracking Overview: This will provide an overview of all assessments for a participant on one page. The only field that must be filled in by the assessor is the scheduled date of assessment (if that date changes during one of the reminder calls), all other information will be pulled from previously completed forms.

## 8. STATISTICAL ANALYSIS

### 8.1 PRIMARY ANALYSES

The study aims to test the hypothesis that compared with placebo, participants receiving zinc supplementation will have significantly 1) lower VACS index scores; 2) higher CD4 cell counts; 3) lower Reynolds risk score and; 4) lower biomarker levels of microbial translocation and inflammation. The primary outcome is improved markers of mortality, as measured by change in VACS index score between baseline and 18 months. The secondary outcomes are slower HIV disease progression, as measured by change in CD4 cell count; improved markers of AMI risk, as measured by the Reynolds Risk Score; and lower biomarker levels of microbial translocation and inflammation.

This study will be conducted under the intention-to-treat principle and thus main analyses will include all participants according to their randomized assignment. Descriptive statistics will be calculated for variables at baseline and each follow-up time point. At baseline, participant characteristics will be

presented by randomized arm to assess whether there are any differences between groups. Spearman correlation coefficients will be obtained to identify pairs of variables that may be collinear ( $r > 0.4$ ) and would therefore not be included together in regression analyses.

The main analysis evaluating the impact of zinc on the primary study outcome (i.e., change in VACS index) will use multiple regression models that include randomization group (i.e., zinc vs. placebo) as the main independent variable. The regression analyses will control for the two block randomization stratification factors: heavy alcohol consumption during the past week and gender. In addition, the models will control for baseline characteristics that differ between groups in order to avoid confounding. Potential confounders of interest, measured at baseline, include demographics, past month alcohol use, age, gender, anti-inflammatory medication use, cardiovascular disease risk factors, HCV status, substance use (e.g., alcohol, smoking, cocaine), CD4 cell count, HIV-1 RNA, duration of awareness of HIV infection, and socioeconomic status. If the data are normally distributed, multiple linear regression models will be used. However, if the distribution is skewed, transformations of the data will be performed (e.g., log transformation). If an appropriate transformation is not identified, a median regression model will be used. The secondary outcomes, including HIV disease progression, as measured by change in CD4 cell count (Aim 2); the Reynolds risk score (Aim 3); and biomarkers of microbial translocation and inflammation (Aim 4) will be analyzed using the same approach described above. A secondary analysis will be conducted using a per protocol approach that includes only those participants who were adherent with their assigned intervention (i.e., taking zinc or placebo 80% of the time).

## 8.2 ADDITIONAL EXPLORATORY ANALYSES

**Effect of zinc over time:** The main analyses will focus on the VACS index, our primary outcome, and other secondary outcomes at the 18 month time point as the primary interest is in evaluating the long-term effects of zinc and it is anticipated that effects will change over time. Additional analyses using generalized linear mixed effects models will be used to incorporate the repeated measures for each outcome in the same model and will test for possible zinc by time interactions (e.g. does the effect of zinc increase over time). The mixed effects models will include subject-specific random intercepts and slopes to account for the correlation due to having repeated observations for each subject. The mixed models will be implemented in SAS PROC MIXED. In addition to the mixed effects model, we will also consider additional confirmatory models such as the general linear model for correlated data using an autoregressive covariance structure.

**Moderators and Mediators:** Additional analyses will also be conducted to evaluate whether the effects of zinc depend on level of alcohol consumption. Models will be fit including a zinc by heavy alcohol interaction term. If the interaction is significant, subsequent stratified analyses will be conducted to evaluate the effect of zinc in each alcohol group. Given the potentially complex role of ART use in the relationship between zinc and each outcome, various analyses will be considered to explore its possible role. First, it is not expected that initiation of ART use during follow-up to differ by randomized arm, however exploratory analyses will be conducted to compare initiation of ART use by randomized group. In addition, longitudinal analyses will be conducted including ART use as a time dependent variable in

order to explore a potential zinc by ART use interaction. If ART use does not appear to be an effect modifier, we will also include it as time will also be included as a dependent covariate to evaluate whether it is a confounder. Lastly, to evaluate ART use as a potential mediator of the relationship between zinc and outcomes of interest, the approach described by Baron and Kenny will be used. To evaluate mediation, the change in magnitude of the zinc effect on our primary outcome, the VACS index (and our other secondary outcomes) in models with and without adjustment for ART use will be focused on. Results will be confirmed using structural equation models (SEMs) to simultaneously model the hypothesized mediated relationships. Fit statistics such as the root mean square error of approximation (RMSEA), Comparative Fit Index (CFI), and the chi-square statistic, will be presented to evaluate the goodness of fit of the SEMs.

Enrollment and Attrition/Missing data: Subjects who meet eligibility criteria and agree to participate will be compared with subjects who were determined to be eligible but declined enrollment on data captured during eligibility assessment. The 2 independent samples t-test and Fisher's exact test will be used to test for statistically significant differences between subjects who enroll and those who do not, and to test for significant differences between subjects lost to follow-up and those who complete it. Missing data patterns will be evaluated including the frequency and percentage of subjects missing for each variable and the distribution of the number of variables missing for subjects. In addition, data collected to the point of lost to follow-up will be compared to the data of those who complete the study to examine missing data mechanisms, e.g., missing completely at random (MCAR), missing at random (MAR), or not missing at random (NMAR). We will consider various approaches to account for missing data such as multiple imputation methods and likelihood-based approaches, if needed. In situations where missing data occurs, we will document the reasons for the missing data whenever possible. The proposed study has accounted for a 20% random noninformative loss to follow-up and will still have sufficient power with this potential loss in size.

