## 2. OVERVIEW OF STUDY DESIGN

### 2.1 STUDY AIMS AND OUTCOMES

138

139 ZINC aims to test the efficacy of zinc supplementation, compared to placebo, to:

140 1. Improve markers of mortality as measured by the change in VACS index between baseline and 18  
141 months—Primary outcome

142 2. Slow HIV disease progression as measured by change in CD4 cell count between baseline and 18  
143 months—Secondary outcome

144 3. Improve markers of AMI risk as measured by the Reynolds risk score at 18 months—Secondary  
145 outcome

146 4. Lower biomarker levels of microbial translocation and inflammation at 18 months—Secondary  
147 outcome

148

149 **2.2 STUDY HYPOTHESES**

150

151 We hypothesize that as compared with placebo, participants receiving zinc supplementation will have  
152 significantly:

153 Hypothesis 1- Smaller change in VACS (Primary);

154 Hypothesis 2- Greater change in CD4 cell counts (Secondary);

155 Hypothesis 3- Lower Reynolds risk score (Secondary);

156 Hypothesis 4- Lower biomarker levels of microbial translocation and inflammation (Secondary).

157

158 **2.3 STUDY DESIGN**

159

160 ZINC is a double-blinded randomized placebo-controlled trial of zinc supplementation (Zinc for  
161 INflammation and Chronic disease in HIV [ZINC]) among HIV-positive heavy drinkers in Russia to  
162 evaluate the efficacy of zinc to 1) improve markers of mortality, as measured by the VACS index; 2) slow  
163 HIV disease progression, as measured by CD4 cell count; 3) improve markers of coronary heart disease  
164 (CHD) risk, as measured by the Reynolds risk score and; 4) decrease microbial translocation and  
165 inflammation, as measured by serum biomarkers. Participants will receive study medication over 18  
166 months, with study visits occurring at 6, 12, and 18 months post enrollment, and shorter medication  
167 adherence visits at 6 weeks, 12 weeks, 9 months, and 15 months. ZINC RCT is nested within the Russia  
168 ARCH cohort of the Uganda, Russia, Boston Alcohol Network for Alcohol Research Collaboration on  
169 HIV/AIDS (URBAN ARCH) Consortium, which aims to understand how alcohol use impacts people  
170 affected by HIV and develop interventions to reduce alcohol use and alcohol and HIV-related

consequences in this population.

[figure not shown]

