# **SECTION 3: STATISTICAL PRINCIPLES**

## **3.1 Confidence intervals and P values**

Statistical tests will be 2-sided and will be performed using a 5% significance test. Confidence intervals will be reported for measures of effect.

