#### Moderators and Mediators:

Additional analyses will also be conducted to evaluate whether the effects of zinc depend on level of alcohol consumption. Models will be fit including a zinc by heavy alcohol interaction term. If the interaction is significant (i.e.  $p<0.10$ ), subsequent stratified analyses will be conducted to evaluate the effect of zinc in each alcohol group.

Given the potentially complex role of ART use in the relationship between zinc and each outcome, various analyses will be considered to explore its possible role. First, it is not expected that initiation of ART use during follow-up to differ by randomized arm, however exploratory analyses will be conducted to compare initiation of ART use by randomized group. In addition, longitudinal analyses will be conducted including ART use as a time dependent variable in order to explore a potential zinc by ART use interaction (we will use  $\alpha = 0.10$  to test interaction). If ART use does not appear to be an effect modifier, we will also include it as time will also be included as a dependent covariate to evaluate whether it is a confounder. Lastly, to evaluate ART use as a potential mediator of the relationship between zinc and outcomes of interest, the approach described by Baron and Kenny will be used. To evaluate mediation, the change in magnitude of the zinc effect on our primary outcome, the VACS index (and our other secondary outcomes) in models with and without adjustment for ART use will be focused on. Results will be confirmed using structural equation models (SEMs) to simultaneously model the hypothesized mediated relationships. Fit statistics such as the root mean square error of approximation (RMSEA), Comparative Fit Index (CFI), and the chi-square statistic, will be presented to evaluate the goodness of fit of the SEMs.

To further assess initiation of ART, we will compare proportions initiating of ART by 18 months by randomized group using the chi-square test and also the logrank test to account for drop out/loss to follow-up.

We will also test zinc by heavy alcohol (past week) interaction.

We will test differences in VACS index components between groups.

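### The exploratory ART mediation analysis reads the change in the zinc coefficient and specifies no indirect effect, no interval for it and no rule for interpreting the change

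*Supplement*

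**What the plan says.** Protocol 8.2, headed "ADDITIONAL EXPLORATORY ANALYSES", and SAP 5.4 (Moderators and Mediators) treat ART use in several ways. The last of these is mediation, where protocol 8.2 reads "the approach described by Baron and Kenny will be used. To evaluate mediation, the change in magnitude of the zinc effect", and SAP 5.4 repeats that "the approach described by Baron and Kenny will be used". The zinc effect on the VACS index and on the secondary outcomes is then compared "in models with and without adjustment for ART use will be focused on". The next sentence adds: "Results will be confirmed using structural equation models (SEMs) to simultaneously model the hypothesized mediated relationships". The output named for those models is RMSEA, CFI and the chi-square statistic.

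Three other statements bear on the point:
- Both documents say "it is not expected that initiation of ART use during follow-up to differ by randomized arm". SAP 5.4 compares ART starts between arms by chi-square and log-rank tests.
- SAP 3.1 states generally: "Confidence intervals will be reported for measures of effect".
- SAP 5.4 sets a significance level of 0.10 for interactions. It sets no corresponding rule for mediation.

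**The concern.** Participants are ART-naive at entry and may start ART during 18 months, so readers may turn to this analysis when they interpret the VACS result. Two features of the stated method make it a weak guide.

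First, the Baron-Kenny sequence conventionally begins with a significant total effect and looks for a treatment effect that shrinks once the mediator is added. If the path through ART ran against the direct effect, the total effect would be smaller and adjustment would enlarge the zinc coefficient. The sequence would tend to stop at its first step or be read as no mediation.

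Second, the quantity the plan focuses on is a difference between two coefficients, with no interval and no stated size that counts. Chance imbalance in ART starts moves that difference even when zinc has no effect on ART.

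**Working it through.** **Inputs from the documents (protocol 2.7.A).** SD of VACS change 25, 100 evaluable per arm, two-sided 0.05, target difference 10, power 80%.

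**Assumed, not in the documents.** ART start rates of 20-50%, ART effect on VACS of -10 to -25, direct zinc effect of -10 or -5, a 10% cut-off for a notable coefficient change, and no unmeasured confounding of ART and outcome.

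**1. The plan's own figure.** The standard error of the difference is 25 × √(2/100) = 3.54. Then 10/3.54 = 2.83, and Φ(2.83 − 1.96) = 80.7% (80.4% by noncentral t). The stated 80% reproduces.

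**2. Opposing path.** Total effect = direct effect + ART effect × (ART rate on zinc − ART rate on placebo). With a direct effect of -10, an ART effect of -15 and ART starts of 30% zinc vs 50% placebo: -10 + (-15)(-0.20) = -10 + 3 = -7. Power for the total effect: 7/3.54 = 1.98, so Φ(0.02) ≈ 51% (50.4% by t). The first step alone therefore stops about half of such trials. With an ART effect of -20 the total is -10 + 4 = -6.

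Simulation with 3,000-4,000 trials per scenario, linear models and direct effect -10. The steps are: total effect, zinc to ART, and ART to outcome, each at p<0.05.

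| ART start, placebo vs zinc | ART effect | Total effect significant | All three steps | Steps plus shrinkage | Indirect-effect 95% interval excludes 0 |
|---|---|---|---|---|---|
| 40% vs 20% | -15 | 50% | 41% | 0% | 75% (Sobel) |
| 40% vs 20% | -20 | 40% | 32% | 0% | 84% (Sobel) |
| 50% vs 30% | -15 | 48-52% | 36-39% | under 0.1% | 72% (Sobel), 82% (Monte Carlo) |
| 50% vs 30% | -20 | 38% | 27% | 0% | 78% (Sobel), 84% (Monte Carlo) |
| 40% vs 30% | -15 | 67% | 18% | 0% | 22% (Sobel) |

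The last row sets a limit: with only a 10-point difference in ART starts, neither approach detects much. In mirror-image scenarios, where zinc raises ART starts, the full steps succeed in 82-95%. The weakness therefore comes from the direction of the path and not from the sample size.

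**3. No mediation.** With equal ART starts, the coefficient change is roughly the ART effect times the chance difference in ART proportions. At 40% in both arms and an ART effect of -15, its SD is about 15 × √(2 × 0.4 × 0.6/100) = 1.04 points.
- Direct effect -10: a 10% change is 1 point. 1/1.04 = 0.96, and the two-sided probability is about 34% (35% simulated).
- Direct effect -5: a 10% change is 0.5 points. 0.5/1.04 = 0.48, giving about 63% (61% simulated).

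Across the assumed scenarios the change exceeds 10% in 15-47% of trials at -10 and in 41-71% at -5. The full steps, including shrinkage, are falsely met in 0.3-2.7%, and the three significance steps alone in 0.5-4.1%. The indirect-effect interval falsely excludes zero in 0.4-4.5% (Sobel) or about 5% (Monte Carlo).

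**The case against.** The strongest reply is that the plan is less bare than it looks.

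- **Intervals.** A reader might infer that the plan offers no interval at all. It does not say that: SAP 3.1 promises intervals for measures of effect, and a structural equation model estimates both paths without needing a significant total effect. What stands is narrower. The indirect effect is never named as a measure of effect, and the models are tied only to fit statistics, which describe neither its size nor its uncertainty.
- **Aim 2.** A reader might infer that Aim 2, "Slow HIV disease progression as measured by change in CD4 cell count between baseline and 18" months, implies an opposing path. It does not. That would require ART starts to depend on CD4 count or progression. The documents state no such rule and expect no arm difference.
- **Shrinkage.** The plan speaks of a change in magnitude without giving a direction. Requiring shrinkage is the conventional reading, so the near-zero detection figures apply only if it is imposed. A coefficient that grows after adjustment would be visible, but the plan does not say how to read it.
- **False mediation.** A reader might infer that the plan will report mediation where none exists. The full steps rarely do so. Only the coefficient change read alone, with the assumed cut-off, reacts often to chance.
- **Existing check.** The chi-square test would usually reveal a 50% vs 30% difference in ART starts: 0.20/√((0.25 + 0.21)/100) = 2.95, and Φ(2.95 − 1.96) ≈ 84%. This covers the zinc-to-ART path only and does not estimate the mediated effect.
- **Confounding.** If progression drives both ART starts and VACS, the interval's detection and error rates above are best case. This objection stands, and the fix should say so.

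**Conclusion.** The point holds as a gap in an exploratory analysis. Neither document provides an indirect-effect estimate with an interval that is read regardless of whether the total effect is significant, and neither says how to interpret the coefficient change.

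If zinc cut ART starts by 20 points, with an ART effect of -15 or -20 and a direct effect of -10, the three significance steps would miss the mediation in roughly 59-73% of trials, against 16-28% for an interval. If ART starts are equal, as the plan expects, the coefficient change is an unreliable signal on its own, while the formal steps keep false findings under 5%. Every ART rate and ART effect here is an assumption, and so is the 10% cut-off.

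The documents do not support saying that the trial's own aims make the method fail. The primary and secondary treatment comparisons do not depend on this analysis.

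**What to change.** In protocol 8.2 and SAP 5.4, replace the Baron-Kenny steps and the change-in-magnitude reading with text to this effect:

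*The indirect effect of zinc through ART use and the direct effect of zinc will each be estimated with a 95% confidence interval (bootstrap, Monte Carlo, or from the structural equation model). They will be reported whatever the sign or significance of the total effect. Any statement about mediation will rest on the interval for the indirect effect, will be labelled exploratory, and will note that it assumes no unmeasured confounding between ART use and the outcome.*

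The planned structural equation models can supply these estimates, and the comparison of ART starts by arm can stay as it is. The cost is a few sentences and a short program, with no new data or participants.
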